### Participating Study Clinics

All five surgical abortion clinics offering second trimester abortion in the province of BC are collaborating in this study. The geographic catchment areas for the clinics include both urban and rural areas, and service through these clinics is provided in both hospital and free-standing publicly-funded outpatient settings.

### Enrollment process

All women presenting to a participating clinic for an abortion of a pregnancy over 12 weeks and under 24 completed weeks receive information on the research study web page [35] at the time they book their appointment, and a study information brochure upon check in. Women consenting to participate complete an initial CSQ. Participants receive their chosen IUC at no cost in addition to a gift card and are randomly allocated using an internet-based randomization service [36], to immediate or planned delayed insertion, with stratification for device, parity and clinic site. This trial has been registered at controlled-trials.com (ISRCTN19506752). A pilot phase study undertook to develop, pilot test and focus group review the CSQ from an existing validated questionnaire [37], adapted for use in our population and for this study, including translation into the three most common non-English languages in our population (Cantonese, Mandarin and Punjabi). A user-friendly internet based format for each of the four languages and sampling times (intake, three, six and 12 month and annually to five years) was implemented.

### Immediate insertion group protocol

Women randomized to immediate insertion have their chosen IUC inserted by their surgeon immediately following the abortion prior to leaving the procedure or operating room. As per standard clinic protocols all women in both groups have polymerase chain reaction (PCR) testing for chlamydia and gonorrhoea prior to their abortion, and receive two grams metronidazole single observed dose as prophylaxis against postoperative infection [38]. Women deemed to be at higher risk of a sexually transmitted infection (as per criteria used by all BC clinics [38]), and those with positive PCR results, receive one gram of azithromycin as well. An ultrasound image of the IUC in situ is recorded. If an ultrasound machine is not immediately available in the operating room, arrangements are made for an ultrasound to be performed to confirm proper IUC position.

### Delayed insertion group protocol

Women randomized to planned delayed insertion are managed as closely as possible to standard practice. Participants are asked to make an appointment for follow-up and IUC insertion at 4 +/-1 weeks after the date of their abortion. All women are offered one month of an alternate contraceptive. An opportunity to return for follow-up and IUC insertion at any study clinic is available to all women, as per recommended post abortion delayed IUC insertion practice. Participants who have travelled over 100 km from a study clinic are asked to make arrangements for insertion in their home community. Study participants experience conditions as close to standard non-study delayed insertion conditions as possible. These women receive a "SmartPayment"^® ^card [39] and a prescription for the IUC. This permits participants to receive the IUC cost-free (as is the case for those able to return to the study clinic for insertion) and for the patient's pharmacy of choice to be reimbursed for the IUC. The participant is also given a requisition for a post-insertion ultrasound. The BC Medical Services Plan provides payment for the IUC insertion and the post-insertion ultrasound. This procedure is designed to as closely as possible emulate the real-life conditions each participant would experience were she not in a research study. This process eliminates possible bias in IUC insertion rate, and thus pregnancy rate, were she to take home a free study IUC or we to courier it to her designated health care provider.

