### Outcome determination

CSQ are offered by mail, email or as a web-based questionnaire at 3, 6 and 12 months and annually to five years following enrollment. The CSQ collect data on expulsion of IUC, effectiveness and satisfaction with contraceptive method and insertion timing assigned, any removal of the IUC, any change to contraceptive method or intention to conceive, any interval pregnancies and their outcomes, and any adverse events. In addition participants are asked to arrange to return to any of the study sites or see their primary health care provider for a follow-up clinical examination at 3, 6 and 12 months following the abortion. Information from clinical visits and CSQ will be used in conjunction with BC administrative health database information to determine outcomes.

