### Analysis methods

We will compare one year pregnancy rates using a chi-squared test declaring significance if p < .05 and provide 95% confidence intervals for the difference in pregnancy rates using the large sample normal approximation for differences in proportions. This simple approach is valid so long as no systematic difference in follow-up occurs between groups. As a check, we will also conduct analysis to account for partial follow-up. Since our outcome definition is essentially composite and the relevant risk periods differ by components, Kaplan-Meier estimates for each component event will be determined and composite estimates will be obtained by summing the estimated cumulative event rates (calculated as 1 - the survival function) at the time-points indicated in our operational definitions. Confidence intervals around the difference in these estimates will be calculated using the bootstrap.

Rates for all secondary outcomes will be calculated for events occurring within one year following abortion, and annually for five years, using the follow-up questionnaires, direct access to clinical follow up visit records, and billing and procedure coding data from the administrative health system databases. Multivariate logistic regression will be used to examine demographic, socioeconomic, and obstetrical factors in relationship to primary and secondary objectives.

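### Only the delayed arm has a planned clinical contact in the first 3 months, so early infection may be recorded more often there, a modest bias toward immediate insertion

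*Protocol article*

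**What the plan says.** All places are in the Methods of the protocol article.

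- **Delayed insertion group protocol:** "Participants are asked to make an appointment for follow-up and IUC insertion at 4 +/-1 weeks after the date of their abortion". The appointment is for follow-up as well as for placing the device. Women who travelled more than 100 km are asked to arrange insertion near home, and for them: "The participant is also given a requisition for a post-insertion ultrasound".
- **Immediate insertion group protocol:** women "have their chosen IUC inserted by their surgeon immediately following the abortion prior to leaving the procedure or operating room". No clinic visit in the following weeks is stated. On imaging: "An ultrasound image of the IUC in situ is recorded". If no machine is at hand in the operating room, "arrangements are made for an ultrasound to be performed to confirm proper IUC position".
- **Outcome determination**, without distinction of arm: questionnaires at 3, 6 and 12 months and then yearly, and a request to return to a study site or "see their primary health care provider for a follow-up clinical examination at 3, 6 and 12 months following the abortion".
- **Analysis methods:** rates for all secondary outcomes are calculated over one year from the abortion, "using the follow-up questionnaires, direct access to clinical follow up visit records, and billing and procedure coding data". The Analysis section lists infection and perforation as adverse events, and expulsion, among the secondary outcomes.

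**The concern.** Between the abortion and 3 months, one arm is asked to attend a clinical visit and the other is not. A mild infection at 3 to 5 weeks can be written down at the delayed arm's visit. In the immediate arm, the same infection enters the data only if the woman seeks care for it or reports it at 3 months. The visit records feed the secondary rates with no stated allowance for this difference.

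The plan accepts the principle for its primary outcome. Analysis methods makes the simple comparison of pregnancy rates conditional on follow-up not differing systematically between groups, and adds a check. For the secondary outcomes, where a difference in scheduled contact is built in, the article describes no corresponding check.

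At stake is part of the safety comparison. The Introduction explains that delay is recommended in order to limit complications, so readers will look closely at the complication rates. Extra detection in the control arm would favour the experimental strategy.

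**Working it through.** **Step 1: scheduled contacts side by side**

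| Time from abortion | Immediate arm | Delayed arm |
|---|---|---|
| Day of abortion | Device placed; scan recorded, or arranged if no machine | Abortion only |
| 4 ± 1 weeks | None stated | Follow-up and insertion visit |
| After the delayed insertion | – | Scan requisition (home-community insertions) |
| 3, 6, 12 months | Questionnaire and examination | Questionnaire and examination |

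One sentence might seem to close the gap: "An opportunity to return for follow-up and IUC insertion at any study clinic is available to all women". It stands in the delayed-arm section, joins follow-up to insertion and refers to delayed-insertion practice, so it most naturally describes the delayed arm.

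**Step 2: which outcomes the extra visit can affect**

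- *Infection and similar events after the abortion:* yes. Every woman is at risk, with or without a device.
- *Expulsion:* no. The visit that places a device cannot detect its loss, and a lost device is still absent at the shared 3-month examination. Taking 3 months as about 12 weeks, that examination falls about 12 weeks after insertion in the immediate arm and 12 − 4 = 8 weeks (7 to 9) in the delayed arm. Counting one year from the abortion also gives immediate devices about 4 more weeks at risk, which does not favour that arm.
- *Scan findings:* no material contrast. Both arms have a scan that checks position after insertion.
- *Pregnancy and sample size:* unaffected; no power input depends on this visit.

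**Step 3: illustration of size, infection only**

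The plan states no infection rate, so there is no planned figure to reproduce. From the documents come 358 women per arm and return for delayed insertion of 65% (the planning value) or 26% (the lowest cited figure). Assumed, and not in the documents, are an equal true infection rate *t* of 2% or 5%, and a share *s* of cases found only if an early visit takes place, of 10%, 30% or 50%. With *r* for the return rate:

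- Recorded rate, immediate arm: *t*(1 − *s*)
- Recorded rate, delayed arm: *t*(1 − *s* + *s r*)
- Spurious difference: *t s r*

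Extremes: 0.02 × 0.10 × 0.26 = 0.00052, and 0.05 × 0.50 × 0.65 = 0.01625.

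Each cell gives the difference in percentage points, then the approximate chance of a significant result favouring immediate insertion at two-sided 5% (2.5% in that direction by chance alone).

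| *t* | *s* | *r* = 26% | *r* = 65% |
|---|---|---|---|
| 2% | 10% | 0.05; 2.8% | 0.13; 3.4% |
| 2% | 30% | 0.16; 3.7% | 0.39; 6.1% |
| 2% | 50% | 0.26; 5.1% | 0.65; 11.5% |
| 5% | 10% | 0.13; 3.0% | 0.33; 4.0% |
| 5% | 30% | 0.39; 4.6% | 0.98; 9.8% |
| 5% | 50% | 0.65; 7.6% | 1.63; 22.8% |

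In events per arm, the extremes are 358 × 0.00052 = 0.2 and 358 × 0.01625 = 5.8. The number of delayed-arm women with the extra contact would be 0.26 × 358 = 93 to 0.65 × 358 = 233.

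The chances use a normal approximation, which is rough at these counts, and they pool the two devices. The return rate may also overstate the extra contact with the study, because some insertions take place in the home community.

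**The case against.** The strongest case on the other side has four parts.

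1. **Shared sources catch most events.** The 3-month questionnaire asks every woman about adverse events, and the linked records cover services, admissions and prescriptions. Only infections that led to no care and were not reported at 3 months would be missed. This stands. It limits the size of the bias but does not remove it.
2. **The visit belongs to the strategy under test.** The delayed arm is deliberately kept close to usual practice. That is a good reason to keep the visit. It does not turn an infection recorded because someone looked into an effect of insertion timing.
3. **This is a condensed article.** Rules on event sources may sit in the full protocol or the analysis plan, and no between-arm test of infection is named. This stands as a caution: the point concerns what the published schedule and source list produce together, not a missing detail.
4. **Setting aside events found only at the 4-week visit would do harm.** Perforation or malposition from delayed insertion would surface there, while the immediate arm's counterparts, seen in the operating room or on its scan, would stay in. This stands, and it rules out any such exclusion from the main comparison.

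A reader might infer more: that immediate insertion will look safer by detection alone, on expulsion and scan findings as well as infection. The documents do not support that. The 4-week visit cannot find an expulsion, both arms have a position scan, and most ascertainment is common to the two arms.

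**Conclusion.** The point holds in a limited form. As published, only the delayed arm has a planned clinical contact between the abortion and the shared 3-month assessments, and the secondary rates draw on visit records regardless of arm. Mild or self-limiting early infection, and similar events that every woman is at risk of, may be recorded more often in the delayed arm. All else equal, this favours immediate insertion.

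The size cannot be derived from the document. The range of 0.05 to 1.6 percentage points rests on assumed infection rates and detection shares: the lower end is negligible and the upper end would matter. True differences in either direction remain possible. The bias concerns secondary outcomes only.

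**What to change.** In Analysis methods:

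- Keep the all-source rates as the main safety comparison, with every insertion-related event in both arms included (perforation, malposition).
- Tag each infection or other non-insertion adverse event by how and when it was first found.
- Add a sensitivity comparison of those events limited to sources scheduled alike in both arms: the 3-, 6- and 12-month questionnaires and examinations, plus records of care the woman sought herself.
- Treat billing or prescription records generated by the 4-week visit as belonging to that visit. Otherwise an infection found and treated there would re-enter through the administrative data.

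The sensitivity comparison is not free of bias either, because some events found at 4 weeks would have surfaced later. Reading it beside the all-source rates shows how far the conclusion depends on the extra visit.

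The cost is one extra data field and slightly fewer events in the sensitivity analysis. No visit, procedure or treatment changes.

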### Outcome determination

CSQ are offered by mail, email or as a web-based questionnaire at 3, 6 and 12 months and annually to five years following enrollment. The CSQ collect data on expulsion of IUC, effectiveness and satisfaction with contraceptive method and insertion timing assigned, any removal of the IUC, any change to contraceptive method or intention to conceive, any interval pregnancies and their outcomes, and any adverse events. In addition participants are asked to arrange to return to any of the study sites or see their primary health care provider for a follow-up clinical examination at 3, 6 and 12 months following the abortion. Information from clinical visits and CSQ will be used in conjunction with BC administrative health database information to determine outcomes.

### Ethical Aspects

This study has received institutional review board approval from the following research ethics boards: the University of British Columbia-Children's and Women's Research Ethics Board (H10-00306), the Interior Health Authority Research Ethics Board (2010-028) and the Vancouver Island Health Authority Clinical Research Ethics Board (C2010-47). A Data and Safety Monitoring Board has been established consisting of an Obstetrician-Gynaecologist, a biostatistician, an expert in Population and Public Health and database linkage research, and an economist specializing in population health pharmaceutical economics, all from Canadian universities outside of BC, and each being independent of all members of the research team. Funding for this study is primarily through grants from the Canadian Institutes for Health Research, with pilot funding and administrative support from the Women's Health Research Institute, and the University of British Columbia. Donation of 385 free Mirena devices was provided by Bayer Inc. as their sole contribution to the research study.

### Analysis

*Primary outcome *will be examined in an intention-to-treat framework as pregnancy rate at one year among women randomized to immediate insertion compared to women randomized to a planned insertion at 4 weeks ("delayed insertion") for each of the two IUC devices. For example, if women in the delayed group present for insertion after the specified 4+/-1 week insertion window, or even at the time of a subsequent abortion or delivery, we will insert the device at the women's request and her assignment for the primary analysis will not change. Similarly if for any reason a woman assigned to the immediate insertion group is unable to have her insertion immediately (for example, should she have an unattended expulsion/delivery of her pregnancy prior to the planned surgical abortion) then insertion will be offered at the time the woman and her physician would normally undertake to do so, and whether or not her insertion ever occurs, her assignment for the purpose of analysis will not change. Thus our primary outcome of pregnancy rate at one year reflects real life conditions.

*Secondary outcomes *include: costs and cost effectiveness, cumulative annual pregnancy rate, device insertion rate, loss to follow-up; continuation of method; adverse events (such as infection or perforation); expulsion; outcomes among those participants who were chlamydia positive at the time of insertion; satisfaction with IUC chosen and with insertion timing assigned. These outcomes will be assessed initially at one year, then annually through the five year device effectiveness period.

### Operational definition for outcome

Although our outcome of one year pregnancy rate is conceptually simple, exact determination of conception dates is clearly infeasible. Consequently our actual outcome definition provides a pragmatic approximation based on the varying exactitude of imputations based on provincial Medical Service Plan billings related to abortions, miscarriages, still births and live births. Subsequent abortions performed within our study clinics for enrolled participants will be noted along with specific clinical information on pregnancy duration. For abortions performed elsewhere such as those for BC university students studying out of province, or those performed by individual physicians at rural or remote hospitals within BC, exact gestation may not be available. In the BC health administrative databases abortions are billed as under 7 weeks for medical abortions, and as under 14 weeks, 14 weeks to under 18 weeks, and 18 weeks and over for surgical abortions. Miscarriages by definition occur anytime under 20 weeks or are classed as still birth when over 20 weeks of gestation. Thus for subsequent pregnancies where the specific gestation is unknown, we will consider a pregnancy to have occurred in the first year according to the following conservative adjustments to one year follow-up dates. (see Table 3.)

**Table 3 T3:** Operational definition of a pregnancy as derived from administrative billing data

Billing Type	Nominal weeks of gestation	Cut-off for operational definition
Abortion (medical)	< 7 weeks*	1 year + 4 weeks
Abortion (surgical)	< 14 weeks	1 year + 6 weeks
Abortion (surgical)	14-18 weeks	1 year + 13 weeks
Abortion (surgical)	≥ 18 weeks	1 year + 17 weeks
Miscarriage	< 20 weeks	1 year + 11 weeks
Still birth	≥ 20 weeks	1 year + 25 weeks
Live birth	Birth date - GA	1 year + XX*

*In Canada, mifepristone is not available. Medication-induced abortions using methotrexate and misoprostol are offered in British Columbia up to a maximum of 49 days (7 weeks) from last menstrual period.

** Where XX = median conceptual age for live births in BC

### Analysis methods

We will compare one year pregnancy rates using a chi-squared test declaring significance if p < .05 and provide 95% confidence intervals for the difference in pregnancy rates using the large sample normal approximation for differences in proportions. This simple approach is valid so long as no systematic difference in follow-up occurs between groups. As a check, we will also conduct analysis to account for partial follow-up. Since our outcome definition is essentially composite and the relevant risk periods differ by components, Kaplan-Meier estimates for each component event will be determined and composite estimates will be obtained by summing the estimated cumulative event rates (calculated as 1 - the survival function) at the time-points indicated in our operational definitions. Confidence intervals around the difference in these estimates will be calculated using the bootstrap.

Rates for all secondary outcomes will be calculated for events occurring within one year following abortion, and annually for five years, using the follow-up questionnaires, direct access to clinical follow up visit records, and billing and procedure coding data from the administrative health system databases. Multivariate logistic regression will be used to examine demographic, socioeconomic, and obstetrical factors in relationship to primary and secondary objectives.

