### Sample Size and Power Calculations

350 women choosing a levonorgestrel-releasing IUC (LNG-IUC, "Mirena^®^", Bayer Inc, Canada), and 366 women choosing a "T" shaped copper IUC with 380 mm^2 ^surface area of copper including copper bands on the "T" arms (CuT380-IUC, "Flexi-T380(+)^®^", Prosan, The Netherlands) will be recruited and randomly allocated to each of two treatment arms: immediate insertion (experimental intervention) vs. planned delayed insertion (recommended care), representing a total enrollment of 716 women into this Phase IIIb RCT (See Table 1). This sample size will provide 90% power in the levonorgestrel stratum to distinguish predicted one year pregnancy rates of 1.2% (immediate) versus 8.7% (delayed) and 80% power for corresponding detection of 2.7% and 9.7% in the copper device users.

**Table 1 T1:** Enrollment Allocation

	Immediate	Delayed	Total
LNG-IUC	175	175	350

CuT380-IUC	183	183	366

Total	358	358	716

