### Estimation of Probable Rates of Pregnancy

The pregnancy rates used in our sample size calculation are justified as follows. The one year failure rate of the LNG-IUC device is known to be 0.1%[32] except in the case of spontaneous expulsion that we conservatively estimate occurs when immediately inserted after second trimester abortion with a probability of 0.05 (observed rate 0.03 by Drey [27] and Cremer [29]). Our estimated post-abortion pregnancy probability in the absence of an IUC is 0.24 [33]. Therefore the estimated pregnancy rate in the immediate insertion LNG-IUC group is expected to be:

In the delayed group, we conservatively estimate 65% of women will return for insertion of the IUC (Stanek found 26% return for planned delayed insertion [28], and Cremer 30%[29]), and we assume (conservatively) the high expulsion rate of the immediate insertion group. These assumptions imply a one-year pregnancy rate of

The one year failure rate for the CuT380-IUC is 1.7%[34]. Using the above formula this yields rates for immediate and delayed insertion of .028 and .102 respectively. Allowing for a loss to follow-up of up to 5% provides conservative estimates of the observed pregnancy rates of .012 and .0874 in the LNG-IUC cohort and .027 and .097 in the CuT380-IUC group.

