### Exclusion Criteria

Women are not eligible if they intend to move from BC within the next year or if they intend to conceive within one year. In addition, if they have a contraindication to the use of the IUC they have chosen (see Table 2) or are currently enrolled in another clinical trial they will be excluded. Post randomization exclusion factors include perforation or excessive bleeding at the time of their abortion or uterine anomaly detected at the time of the abortion procedure. These exclusions are designed to be only those which, in real life, would preclude a woman from being able to choose this method of contraception. This study has no minimum age criteria for enrollment.

**Table 2 T2:** Inclusion and Exclusion Criteria

*Inclusion Criteria - This study will be offered to women at the study sites who meet all of the following criteria: *
Have completed informed consent for an abortion over 12 and under 24 weeks gestational age.
Have chosen an IUC (either LNG-IUC or CuT380-IUC) for contraception post abortion.
Are residents of British Columbia registered with the Medical Services Plan health care system.

Exclusion Criteria

Intention to move from BC within the next year
Intention to conceive within the next year
Uterine cavity anomalies causing distortion of the endometrial canal including fibroids of more than 5 cm, excluding repaired uterine septum
Current untreated PID, Chlamydia, gonorrhea, cervicitis or lower genital tract infection (recent infection is not a contraindication to IUC insertion[35])
Wilson's Disease (if choosing a CuT380-IUC)
Undiagnosed abnormal uterine bleeding
Known uterine or cervical malignancy or cervical dysplasia
Known or suspected progestin-dependent neoplasia, including breast cancer (if choosing a LNG-IUC)
Active liver disease or dysfunction (if choosing a LNG-IUC)
Actual benign or malignant liver tumours (if choosing a LNG-IUC)
Hypersensitivity to levonorgestrel or any of the other ingredients in the formulation or component of the container components of Mirena^® ^(if choosing a LNG-IUC)
Bacterial endocarditis
Established immunodeficiency (HIV positivity is not an exclusion unless immunodeficient)
Acute malignancies affecting blood or leukemias
Recent trophoblastic disease while hCG levels are elevated
Currently enrolled in another investigational study

Post Randomization Exclusion Criteria

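### Equal loss to follow-up protects the one-year chi-squared test, but not the crude pregnancy rates, their difference or its confidence interval, which the plan also calls valid

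*Protocol article*

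**What the plan says.** Under Analysis methods, the one-year pregnancy rates are compared by a chi-squared test, "declaring significance if p < .05", with a 95% interval for the difference in proportions from the large-sample normal approximation. The article then says of this pair: "This simple approach is valid so long as no systematic difference in follow-up occurs between groups". As a check, it adds Kaplan-Meier estimates for each type of pregnancy event, summed at the operational cut-offs of Table 3, with a bootstrap interval for the difference.

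Under Estimation of Probable Rates of Pregnancy, the sample size rests on rates already reduced for loss. For the LNG device it says: "Allowing for a loss to follow-up of up to 5% provides conservative estimates of the observed pregnancy rates of .012 and .0874". The copper rates go from .028 and .102 to .027 and .097. The power statement uses these reduced rates: "90% power in the levonorgestrel stratum to distinguish predicted one year pregnancy rates of 1.2% (immediate) versus 8.7% (delayed").

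For later years, Analysis methods says only: "Rates for all secondary outcomes will be calculated for events occurring within one year following abortion, and annually for five years". Under Exclusion Criteria, the screen for migration covers one year: "Women are not eligible if they intend to move from BC within the next year".

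**The concern.** The two sections do not agree on what equal loss does. The sample-size section expects observed rates below the true ones when both arms lose the same share of women. The analysis section treats equal loss as sufficient for the whole crude approach, interval included.

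If both arms lose the same fraction and the pregnancies of lost women go unseen, each observed rate is the true rate times roughly one minus that fraction, and so is the difference. Under the null both sides shrink alike, so the test keeps its size. Under a real effect, the estimate and its interval are centred too close to zero. The trial would then carry a headline difference that is slightly too small, supported by a sentence claiming a property that only the test has. Loss accumulates with time, so the same practice would matter more if it were carried into the cumulative rates to five years.

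**Working it through.** **Inputs** (Estimation of Probable Rates of Pregnancy; Table 1): device failure f = 0.001 (LNG) or 0.017 (copper); expulsion probability 0.05; pregnancy probability without a device 0.24; return for delayed insertion 0.65; loss up to 5%; 175 women per arm (LNG) and 183 per arm (copper).

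**1. Rates before loss.** The displayed LNG formulas are not legible in the text reviewed. The following reconstruction reproduces the stated values.
- Immediate = 0.95 × f + 0.05 × 0.24
- Delayed = 0.65 × immediate + 0.35 × 0.24
- LNG: 0.95 × 0.001 + 0.012 = 0.01295; 0.65 × 0.01295 + 0.084 = 0.0924; difference 7.95 points.
- Copper: 0.95 × 0.017 + 0.012 = 0.02815; 0.65 × 0.02815 + 0.084 = 0.1023; difference 7.41 points. The article states .028 and .102.

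**2. The loss allowance.** Multiplying by 0.95:
- LNG: 0.0123 and 0.0878 (stated .012 and .0874; 0.092 × 0.95 = 0.0874 if rounded first).
- Copper: 0.0267 and 0.0972 (stated .027 and .097).

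The factor 0.95 fits all four figures. Dropping lost women from the denominator would have left the rates unchanged. The allowance therefore implies that lost women stay in the denominator with no observed pregnancy.

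**3. Stated power.** Two proportions, pooled variance, two-sided 0.05, no continuity correction: 0.902 for LNG (stated 90%) and 0.795 for copper (stated 80%). With no loss these would be 0.918 and 0.822. The loss is thus already paid for in the power.

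**4. The test.** Simulation with 175 per arm, a 5% event rate and equal loss of 0%, 5% or 20% gives a type I error of about 0.049 each time. On the test, the article's sentence holds.

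**5. The estimate at one year, 5% equal loss.**

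| | True difference | All lost at start (×0.95) | Loss spread over the year (×about 0.975) |
|---|---|---|---|
| LNG | 7.95 | 7.55 | 7.75 |
| Copper | 7.41 | 7.04 | 7.23 |

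The shortfall is 0.2 to 0.4 points. If all pregnancies in lost women are missed, the risk ratio is unchanged.

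**6. Years two to five, illustration only.** Assumptions, none of them in the article: women with and without a device keep yearly risks of 0.001 and 0.24, nobody switches, loss is a constant yearly fraction, and crude proportions are used. Without loss, the five-year risk is 1 − 0.999⁵ = 0.0050 with a device and 1 − 0.76⁵ = 0.7465 without.
- Immediate: 0.95 × 0.0050 + 0.05 × 0.7465 = 0.0421
- Delayed: 0.65 × 0.0421 + 0.35 × 0.7465 = 0.2886
- Difference: about 24.7 points

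With event hazard l and loss hazard m, the crude proportion in each group is l/(l+m) × (1 − exp(−5(l+m))). At 5% annual loss this gives 0.0044 and 0.6772, hence 0.0380 and 0.2618, a difference of 22.4 points and a shortfall of about 2.3. At 2% and 10% annual loss the shortfall is about 0.9 and 4.4 points.

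**The case against.** The strongest reply is that this is a small point of wording. Five per cent is an upper bound, linkage to provincial records is meant to keep loss low, the bias is towards no difference, and the power calculation absorbs it. The sentence after the disputed one commits to an analysis for partial follow-up with a bootstrap interval, so the adjusted result will exist. All of this stands, and it keeps the point modest. It does not make the interval valid in the sense claimed, and it leaves the crude difference as the headline.

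Several stronger readings are tempting, but the article does not support them:
- **That the plan counts lost women as not pregnant.** No analysis rule says so. It is inferred from the 0.95 step.
- **That crude, uncensored proportions are planned to year five.** The article is silent on denominator and censoring there. That detail may sit in an analysis plan not shown, and the validity sentence concerns one-year rates only.
- **That the five-year error is large and known.** Running the blended 9.2% forward as one constant hazard gives 38.4% in the delayed LNG arm and a difference of 32.1 points. The article builds that rate from a mixture of women with and without a device. Carrying the mixture forward gives 28.9% and 24.7 points. The annual loss is assumed in either case.
- **That leaving the province means loss.** Questionnaires by mail, email or web ask about pregnancies to five years.
- **That the economic analysis is biased by a known amount.** The article does not say that it uses the crude proportion.
- **That loss differing by arm contradicts the plan.** The sentence expressly excludes that case.

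**Conclusion.** The point holds in a limited form. The article attributes validity under equal loss to the whole crude approach, while its own loss allowance shows that only the test has it. At one year the difference would be understated by at most about 0.4 points in either device stratum, a relative 5%, and by about half that if loss is spread over the year. This rests on the article's upper bound of 5% loss and on pregnancies after loss going unseen. The stated power needs no change.

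For years two to five, only the direction can be argued: loss accumulates, and the migration screen covers the first year only. The 2.3-point figure (0.9 to 4.4) depends on every assumption in step 6 and should be read as an illustration.

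**What to change.** - Keep the chi-squared test, and reword the validity sentence so that it covers the test only.
- Report the already planned follow-up-adjusted estimate, with its bootstrap interval, as the main one-year rate and difference instead of only as a check.
- Use the same estimator if annual cumulative pregnancy rates are reported to year five.
- Estimate it as the cumulative incidence of first pregnancy, with event types as competing events, read at the Table 3 cut-offs (shifted by whole years for later years). Summing separate Kaplan-Meier complements can overstate the total. With two equal components, each censored at the other, a true 9.24% becomes 2 × (1 − √(1 − 0.0924)) = 9.5%.
- Use the claim or event date as the time scale, and censor at the last date on which pregnancies could be ascertained from any source: linked data, clinic records or questionnaire. Back-dating events to conception while counting women at risk until departure would treat conceptions shortly before departure as event-free time and bring back a downward bias.

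The cost is a few sentences in the analysis section, a little more programming, and a headline estimate slightly less simple to explain. Design and sample size are unaffected.
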